
### Study outcomes and measures

The primary outcome is a binary measure of *safe disposal of child feces,* as defined by the WHO/UNICEF Joint Monitoring Programme for Water Supply and Sanitation (JMP). The updated JMP definition describes safe disposal as encompassing two distinct behaviors based on the last time the child defecated: 1) child used the toilet/latrine or 2) caregiver put/rinsed the child’s feces into the toilet/latrine [36]. JMP defined safe disposal of child feces is assessed in both the baseline and endline cross-sectional samples. The primary caregiver of the child < 5 years old (< 5 years at time of survey for baseline; < 5 years at time of intervention delivery for endline) in the household is asked “The last time [NAME OF CHILD] defecated, where did [NAME OF CHILD] defecate?” If the caregiver reports anything except “in latrine” then the following question is asked “Where was [NAME OF CHILD]‘s feces disposed?” A child’s feces are deemed safely disposed if the child defecated in the latrine or if the caregiver disposed of the child’s feces into the latrine.

We recognize that the primary outcome is subject to response bias since it is measured using caregiver self-report. However, asking a respondent to report on the “last time” a behavior took place rather than the “usual” practice is a more robust approach, as demonstrated for other sanitation practices such as latrine use [37]. This is also the approach taken by the JMP. If a caregiver reports “do not know” for the two questions assessing safe disposal, however, then the caregiver will be asked to report on the “usual” practice instead. We anticipate this case to be rare based on previous research conducted in Odisha [26].

Secondary outcomes include household fecal contamination measured by *E. coli* enumeration from collected drinking water and hand rinse samples; other CFM practices such as material used to handle child feces; child latrine use among children up to age 10; psychosocial factors related to safe disposal and child latrine training measured by RANAS questionnaires; and caregiver received social support for CFM. Both the RANAS and social support questionnaires were developed based on qualitative formative research and revised through cognitive interviews. The social support items measure informational, instrumental, and emotional support pertaining to CFM and were adapted from several validated metrics [38–42]. These secondary outcomes are also assessed at both baseline and endline.

### Sample size

#### Trial

The sample size calculation used to determine the number of trial villages was based on the primary outcome of interest: caregiver-reported safe disposal of child feces during the child’s last defecation event for children < 5 years. We used a version of formula five from Rutterford, Copas [43] for a standard parallel-group, two-arm study design with a binary outcome and cluster-level analysis. Formula parameters came from Gram Vikas provided data and previous sanitation studies conducted in Odisha. We estimated an average of 9 eligible households per village (i.e. households with a latrine and at least one child < 5 years) using Gram Vikas village-level survey data and initial baseline data. The baseline prevalence of safe child feces disposal was estimated to be 40.7% based on the matched cohort sub-study in 2015 to 2016 which examined CFM practices of caregivers residing in MANTRA villages in Ganjam and Gajapati districts, the same context as this trial [26]. An intra-cluster correlation (ICC) of 0.103 and 10% loss to follow-up were derived from a sanitation behavior change trial conducted in Puri district, Odisha in 2017 to 2019 [44]. Lastly, we selected a 15% increase in safe child feces disposal as both a meaningful and reasonable level of behavior change. With a baseline prevalence estimate of 40.7%, a 15% change indicates a behavioral shift where the majority of caregivers practice the desired behavior. Assuming an average of 9 eligible households per village, 40.7% baseline prevalence of safe child feces disposal, an ICC of 0.103, 10% loss to follow-up, 80% power, and a significance level of 0.05, we calculated a sample size of 37 villages per arm to detect a minimum 15% change in the primary outcome (corresponding to a prevalence ratio of 1.37). However, we realized during baseline data collection that the cluster sizes greatly varied. We accounted for this variation in cluster size by repeatedly resampling 37 villages per arm from the selected 74 villages. The median effect size that can be detected with 80% power is 16% across simulations. The sanitation behavior change trial in Puri achieved a 15.2% change in safe child feces disposal, making a 16% change attainable [45].

#### Environmental sampling

For environmental sampling, the sample size will be based on logistical feasibility to ensure that samples can be processed in the laboratory on the same day of collection. As a result, only villages that have a driving time from the laboratory of two to three hours or less will be included in sample collection. Additionally, sample collection will be limited to a maximum of 15 households per village. In villages that have more than 15 households with children < 5 years, households for sample collection will be randomly selected. The procedure followed at endline will be similar to the procedure followed at baseline.

#### Process evaluation

Surveys will be completed in a subset of intervention villages, dependent upon resources and travel logistics, to document fidelity and reach for each type of intervention activity delivered. In-depth interviews (IDIs) will be conducted with both Gram Vikas mobilizers and participants to capture their perspective and feedback on the intervention, as well as contextual factors that impacted delivery. Approximately 30 caregivers and each Gram Vikas mobilizer will be interviewed. More or fewer participants may be interviewed depending on saturation of findings. The caregivers will be purposively selected based on certain characteristics, such as their child’s age, in order to capture a range of perspectives. To act as a check on delivery and as another measure of reach, the endline trial survey will include questions for intervention households about participation in the activities. To assess spillover, control households will be asked questions about whether or not any activities related to CFM took place in their village and if they have ever heard of or seen a latrine training mat.

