## Methods

### Study design

Evaluation of the CFM intervention follows a cluster randomized controlled trial design. Following a baseline survey, we used stratified randomization to allocate 74 villages to either the intervention or control arm on a 1:1 basis. Approximately four to six months after intervention delivery, we will conduct an endline survey in the study villages among all eligible consenting caregivers of children < 5 years old (at the time of intervention delivery), along with environmental sampling in a sub-set of households to measure fecal contamination. Effectiveness of the intervention will be assessed on an intention-to-treat basis by comparing the proportion of households in intervention and control villages that report safely disposing of their child’s feces (either by the caregiver disposing of the child’s feces into the latrine or the child using the latrine) the last time the child defecated. A process evaluation will be conducted during intervention delivery to provide targeted feedback to the implementing team and to measure intervention fidelity and reach. We will also conduct in-depth interviews post implementation with the Gram Vikas mobilizers and a sub-set of caregivers who participated in the intervention to elicit feedback on what they liked and did not like about the intervention and to identify recommendations for future implementations.

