## Village selection and random allocation

We randomly selected 74 villages from a sample frame of 501 MANTRA villages in Ganjam and Gajapati districts. Following baseline data collection, author [name] used stratified randomization to allocate villages into intervention or control arm on a 1:1 basis (Fig. 1). A computer-based random number generator was used to complete the allocation. Villages were categorized into one of five distinct geographic-demographic (‘geo-demo’) groups, which served as the stratification variable to ensure balance on a wide range of factors. Villages in each ‘geo-demo’ group have a distinct set of characteristics with regard to their geography (coastal, hilly, tableland, etc.), predominant religion and caste, village size, market access and other characteristics. The ‘geo-demo’ groups mostly align with the ‘block’ level administrative unit (a district subdivision), with several blocks falling under each group. As such, three of the ‘geo-demo’ groups are located entirely in Ganjam district while the remaining two are in Gajapati district. We used replacement re-randomization to ensure balance on two a priori specified variables: number of eligible households per village and village-level baseline reported safe disposal of child feces. We used the Mann-Whitney U Test to test if the distribution of villages on these two variables was not significantly different between the study arms. We also used an independent samples t-test to test if the mean baseline reported safe disposal of child feces was not significantly different between the study arms. The a priori balance criteria were met with the first randomization attempt. Participants and study investigators will not be blinded to village treatment assignment.

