### Data and sample collection

#### Trial

Baseline and endline data collection will be carried out by a team of enumerators and supervised by a local research manager. All team members will be fluent speakers of the local language Odia. For baseline data collection, we conducted a week-long training followed by several days of pilot-testing in non-trial villages, and the same will be done before endline. Throughout the training, team members provide critical feedback on both data collection logistics and the survey tool, especially with regard to question construction (ease of comprehension, colloquial phrasing, etc.), Odia translation, skip patterns, and more (see Supplemental File 2 for the baseline survey tool). For endline data collection, the team will not be informed of village intervention status, but it may be possible for them to infer due to the visible components of the intervention or survey questions related to the intervention.

During both baseline and endline data collection, the enumerator teams will attempt to survey all eligible households within the study village. The target respondent is the primary caregiver of the child < 5 years old. If the primary caregiver is not available then a secondary caregiver is asked to participate. After confirming eligibility and obtaining verbal consent from the participant, the enumerator will conduct the survey. Following the survey, the enumerator will ask to observe the household’s latrine and bathing room and complete a structured spot-check.

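### The endline survey is described with different questions for each arm: a disclosed but partly avoidable way for enumerators to learn the arm

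*Protocol article*

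**What the plan says.** All references are to the protocol article.

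- **Sample size, Process evaluation.** Two sets of endline items are described. For one arm, "the endline trial survey will include questions for intervention households about participation in the activities". For the other, "control households will be asked questions about whether or not any activities related to CFM took place in their village", and whether they know of the latrine training mat.
- **Data and sample collection, Trial.** "For endline data collection, the team will not be informed of village intervention status". The same sentence then concedes that "it may be possible for them to infer due to the visible components of the intervention or survey questions related to the intervention".
- **Village selection and random allocation.** "Participants and study investigators will not be blinded to village treatment assignment".
- **Study outcomes and measures.** The authors recognize that "the primary outcome is subject to response bias since it is measured using caregiver self-report". The outcome rests on two questions put to the caregiver by the enumerator.
- **Study design.** Allocation is by village: "we used stratified randomization to allocate 74 villages to either the intervention or control arm on a 1:1 basis".

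The article does not say where the arm-related items sit in the questionnaire or what triggers them. It mentions no separate interviewer or later visit for them.

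**The concern.** Withholding village status from the endline team is the only masking described. Investigators and caregivers know the arm, and the primary outcome is what a caregiver tells an enumerator. The intervention contains group commitments, goal trackers and certificates, so intervention caregivers already have a reason to report the promoted behavior. An enumerator who also knows the arm may probe or code answers differently. The most plausible direction of such a bias favors the intervention, and the planned analysis could not remove it.

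A questionnaire whose items depend on assigned arm shows the arm once those items appear. Some routes to the arm, such as hardware in the home, are hard to avoid. The choice of survey items is under the sponsor's control.

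There is also a measurement cost. Survey-reported participation is described only for intervention households, and village activity and mat awareness only for control households. Exposure is then not measured on one scale, although the plan wants both reach and spillover and foresees a per-protocol analysis if participation varies.

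**Working it through.** **1. The texts side by side.** The items are described by arm (intervention households, control households). The enumerators are not told the arm. The plan itself names survey questions as a route to the arm. No sentence gives a countermeasure. These points come directly from the sections cited above.

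**2. How far one interview reaches.** Allocation is by village and the Sample size section assumes 9 eligible households per village, or 9 × 0.9 = 8.1 after 10% loss. Suppose that one enumerator did every interview in a village and the arm-related items came last. Only the first outcome interview would then precede any revealing item:

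- (9 − 1)/9 = 89% of interviews done knowing the arm;
- (8.1 − 1)/8.1 = 88% with the loss applied.

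This is an upper end. A team working in parallel would lower it. The same arithmetic applies to a common module whose answers reveal the arm, so ordering within a household protects only in part.

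**3. The plan's own sample size, reproduced.** Inputs: p1 = 0.407, p2 = 0.557, ICC 0.103, 80% power, α = 0.05 (two-sided assumed).

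- n per arm = (1.96 + 0.8416)² × [0.407 × 0.593 + 0.557 × 0.443] / 0.15² = 170.3
- design effect = 1 + (8.1 − 1) × 0.103 = 1.731
- villages per arm = 170.3 × 1.731 / 8.1 = 36.4, rounded up to 37
- prevalence ratio = 55.7/40.7 = 1.37

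Both stated figures (37 and 1.37) reproduce. Nothing in this point changes them.

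**4. Illustration of total differential reporting bias.** The plan gives a 16-point detectable effect at 80% power once varying cluster size is allowed for. This implies SE = 0.16/(1.96 + 0.8416) = 0.0571. With no true effect and a reporting shift b in favor of intervention, the chance of a significant result is P(|Z + b/SE| > 1.96).

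| Assumed shift b | SE 5.7 points (from the 16-point effect) | SE about 5.3 points (from 37 villages × 8.1 households, ICC 0.103) |
|---|---|---|
| 0 | 5% | 5% |
| 3 points | 8.2% | 8.7% |
| 5 points | 14.1% | 15.6% |

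The second SE is √{[p1(1 − p1) + q(1 − q)] × 1.731 / (8.1 × 37)} with q = p1 + b, which gives 0.0531 and 0.0532 for the two shifts. The shifts are assumptions. They stand for reporting bias from every source, and the documents give no way to isolate the share due to arm-specific questions.

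**The case against.** The strongest reply is that the authors already say this. They name survey questions as a route to the arm, state that others are unblinded, and call the outcome prone to response bias. That stands: this is an acknowledged limitation. Disclosure does not supply a safeguard, however, and none is stated.

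A reader might infer three stronger things that the documents do not support.

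- *The enumerator must know the arm in order to give the right module.* The article says which households get which questions, not what triggers them. Data management describes programmed skip patterns, so branching on answers is possible. The endline tool is not shown; only the baseline tool is cited as a supplement.
- *Participation questions prime the caregiver before the outcome items.* The order of items is not given, and a journal article need not give it. The order may be sound in practice.
- *The false-positive rates above are the price of this feature.* They are not. Unblinded caregivers could shift their reports whatever the survey layout.

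It is also fair to say that a common module does not preserve masking across a village. The first caregiver who reports attending meetings or receiving a mat reveals the arm for later interviews there, and visible hardware may do so anyway. This limits the benefit and is the reason for deferring the module where feasible. Finally, the latrine spot-check already follows the survey in the plan, so no change is needed there.

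**Conclusion.** The point holds as a disclosed, partly avoidable weakness. As described, the endline items differ by arm, the enumerators are meant not to be told the arm, and no mitigation accompanies the admission that the questions may reveal it. A second consequence, which needs no assumption about bias, is that survey-reported participation and spillover are not measured with the same items in both arms.

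The size of any bias from this feature is unknown. The upper-end exposure (about 8 of 9 interviews in a village) assumes one enumerator per village. The 8% and 14% figures assume total shifts of 3 and 5 points and serve only to show that modest differential reporting would matter at this trial's precision. The conclusion rests on the article's wording; the endline tool could show that the risk is already reduced.

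**What to change.** Before endline, replace the two arm-specific sets with one identical module for every household in both arms: any CFM activity in the village, any attendance, and having heard of, seen or received a latrine training mat. Branch on the answers, not on assigned arm. Place the module after the primary outcome questions. Where feasible, defer it until all outcome interviews in that village are complete, since one household's answers reveal the village's arm. Analyze the module by arm, for reach in intervention villages and spillover in control villages, and state the arrangement beside the existing caveat on enumerator masking.

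The cost is editing the ODK form and one or two extra questions per household. Deferral may also need a second short contact, which is why it is suggested only where feasible. The sample size and the planned primary model do not change. The change closes one route to the arm; visible hardware and caregivers' own knowledge of their arm remain and should still be reported as limitations.

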## Village selection and random allocation

We randomly selected 74 villages from a sample frame of 501 MANTRA villages in Ganjam and Gajapati districts. Following baseline data collection, author [name] used stratified randomization to allocate villages into intervention or control arm on a 1:1 basis (Fig. 1). A computer-based random number generator was used to complete the allocation. Villages were categorized into one of five distinct geographic-demographic (‘geo-demo’) groups, which served as the stratification variable to ensure balance on a wide range of factors. Villages in each ‘geo-demo’ group have a distinct set of characteristics with regard to their geography (coastal, hilly, tableland, etc.), predominant religion and caste, village size, market access and other characteristics. The ‘geo-demo’ groups mostly align with the ‘block’ level administrative unit (a district subdivision), with several blocks falling under each group. As such, three of the ‘geo-demo’ groups are located entirely in Ganjam district while the remaining two are in Gajapati district. We used replacement re-randomization to ensure balance on two a priori specified variables: number of eligible households per village and village-level baseline reported safe disposal of child feces. We used the Mann-Whitney U Test to test if the distribution of villages on these two variables was not significantly different between the study arms. We also used an independent samples t-test to test if the mean baseline reported safe disposal of child feces was not significantly different between the study arms. The a priori balance criteria were met with the first randomization attempt. Participants and study investigators will not be blinded to village treatment assignment.

### Data and sample collection

#### Trial

Baseline and endline data collection will be carried out by a team of enumerators and supervised by a local research manager. All team members will be fluent speakers of the local language Odia. For baseline data collection, we conducted a week-long training followed by several days of pilot-testing in non-trial villages, and the same will be done before endline. Throughout the training, team members provide critical feedback on both data collection logistics and the survey tool, especially with regard to question construction (ease of comprehension, colloquial phrasing, etc.), Odia translation, skip patterns, and more (see Supplemental File 2 for the baseline survey tool). For endline data collection, the team will not be informed of village intervention status, but it may be possible for them to infer due to the visible components of the intervention or survey questions related to the intervention.

During both baseline and endline data collection, the enumerator teams will attempt to survey all eligible households within the study village. The target respondent is the primary caregiver of the child < 5 years old. If the primary caregiver is not available then a secondary caregiver is asked to participate. After confirming eligibility and obtaining verbal consent from the participant, the enumerator will conduct the survey. Following the survey, the enumerator will ask to observe the household’s latrine and bathing room and complete a structured spot-check.

#### Environmental sampling and lab analysis

Household drinking water and hand rinse sample collection will be carried out during the baseline and endline data collection period by a team of enumerators trained in sterile collection techniques. For drinking water samples, enumerators will instruct caregivers to retrieve drinking water in the way that they would for a young child and pour it into a sterile Whirl-pak bag (Nasco, Fort Atkinson, WI, USA). Drinking water storage containers (if applicable) will also be observed by enumerators and any water treatment practices for the sampled water will be recorded. For hand rinse samples, a sample will be collected from the youngest child in the household who is < 5 years old, upon caregiver consent. If the youngest child is not available, then the hand rinse sample will be taken from an older child in the household who is also < 5 years old. If no child is available or the caregiver does not consent, the hand rinse sample will be requested from the caregiver. Prior to sample collection, the enumerators will observe the presence of any dirt on hands or under fingernails and record how much time has passed since the hands were last washed. To collect the hand rinse sample, the person being sampled will be asked to put each hand, one at a time, in a Whirl-pak bag pre-filled with 200 ml of sterile distilled water for 20 s while the enumerator massages the hand through the plastic bag. Collected samples will be stored in a cooler with ice packs for transport back to the laboratory. The samples will then be processed by trained lab technicians using membrane filtration techniques, and plates will be incubated to enumerate *E. coli* in the collected samples.

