**Methods:**

The intervention consists of six behavior change strategies together with hardware provision: wash basin and bucket with lid to aid safe management of soiled nappies and a novel latrine training mat to aid safe disposal and latrine training. The intervention will be offered at the village level to interested caregivers of children < 5 years of age by a community-based organization. Following a baseline survey, 74 villages were randomly allocated to either intervention or control arm. The primary outcome is caregiver reported safe disposal of child feces after last defecation, either by the caregiver disposing of the child’s feces into the latrine or the child using the latrine, measured approximately four to six months following intervention delivery. Secondary outcomes include fecal contamination of household drinking water and the childs’ hands. A process evaluation will also be conducted to assess intervention fidelity and reach, and explore implementer and participant feedback.

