#### Environmental sampling

We will also use GEE models with robust standard errors that account for village level clustering to analyze if the intervention had an impact on environmental contamination based on collected environmental sampling data from drinking water and hand rinse samples. Separate models will be created for drinking water contamination and hand contamination. Separate models will also be run to analyze the binary outcome of prevalence of *E. coli* as well as the continuous outcome of log *E. coli* concentration. *E. coli* concentration data will be log transformed prior to analysis. If any baseline imbalance is found in contamination levels between intervention and control villages, then this will be adjusted for in final models.

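### The hand outcome is stated as contamination of the child's hands, but caregiver samples can replace child samples and the hand models do not separate the two

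*Protocol article*

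**What the plan says.** All references are to the protocol article.

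- **Abstract, Methods.** The outcome is named by person: "Secondary outcomes include fecal contamination of household drinking water and the childs’ hands".
- **Study outcomes and measures.** The same outcome is household fecal contamination by *E. coli* "enumeration from collected drinking water and hand rinse samples". Whose hands are rinsed is not stated.
- **Environmental sampling and lab analysis** (under Data and sample collection). There is a three-step order. First, "a sample will be collected from the youngest child in the household who is < 5 years old, upon caregiver consent". Second, "If the youngest child is not available, then the hand rinse sample will be taken from an older child in the household", provided that child is also under 5. Third, "If no child is available or the caregiver does not consent, the hand rinse sample will be requested from the caregiver".
- **Environmental sampling** (under Data analysis). "Separate models will be created for drinking water contamination and hand contamination". Each is then analysed as *E. coli* prevalence and as log concentration. Beyond village clustering, the only adjustment named is this: "If any baseline imbalance is found in contamination levels between intervention and control villages, then this will be adjusted for in final models".
- **Inclusion/exclusion criteria.** An endline household qualifies if it had a child under 5 when the intervention was delivered. Hand rinses from children are limited to those under 5.
- **Village selection and random allocation.** Participants and investigators are not blinded to village assignment.

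**The concern.** A reader of the abstract expects an effect on children's hands. The sampling rule can fill some households' hand result with an adult's, and the analysis section gives no instruction to keep those results apart.

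The two kinds of sample need not be interchangeable. The Background describes ground contact and hand-to-mouth behavior as features of young children, and it counts washing of the caregiver's and of the child's hands among the points of exposure. Caregivers are also the people the intervention addresses directly, so its effect on their hands may be larger or smaller than its effect on the child's. The rinse volume is the same 200 ml for everyone, so counts per sample also reflect hand size.

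What is at stake is the interpretation of one secondary outcome. The Discussion presents the trial as the first cluster randomized evaluation of a dedicated child feces management intervention on household fecal contamination, so the hand estimate is likely to be read and cited. It should be clear whose hands it describes.

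**Working it through.** The plan gives no figure for the hand outcome: no expected prevalence or concentration, no substitution rate and no power statement. Environmental sampling is sized on logistics alone. There is therefore nothing to reproduce. The check consists of a reading of the text and an illustration on assumed values.

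**1. Do the sections agree?** The abstract says child. The outcomes section names no person. The collection section says child if possible, otherwise caregiver. The analysis section says hands. No section restricts the hand models to children or adds a person-sampled term, so the text as it stands yields a mixture.

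**2. Will the fallback be used?** Endline follows delivery by about 4 to 6 months. Assume child ages uniform over 60 months and read the rinse age limit as age at sampling. The share of children who were under 5 at delivery and have since turned 5 is then 4/60 = 7% to 6/60 = 10%. This is a share of children. Only a household with no other child under 5 moves to the caregiver, so the household share from ageing alone is lower. Absence and refusal add to it. Baseline eligibility was under 5 at survey, so the ageing route exists only at endline, and the baseline and endline mixes may differ.

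**3. Log10 scale, no true effect.** False difference = (difference in caregiver share between arms) × (child-caregiver gap). Assumed gap: 0.5 log10.
- Share difference 0 points: 0 × 0.5 = 0.
- 10 points: 0.10 × 0.5 = 0.05 log10.
- 20 points: 0.20 × 0.5 = 0.10 log10.

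**4. Binary scale, no true effect.** Arm prevalence = (1 − c) × p_child + c × p_caregiver, where c is the caregiver share in that arm. All values are assumed.
- Child 50%, caregiver 30%, c = 10% in both arms: 0.48/0.48, prevalence ratio (PR) 1.00.
- Same prevalences, control 10%, intervention 20%: 0.46/0.48 = 0.958.
- Same, control 10%, intervention 30%: 0.44/0.48 = 0.917.
- Same, control 20%, intervention 10%: 0.48/0.46 = 1.043.
- Child 40%, caregiver 50%, control 10%, intervention 30%: 0.43/0.41 = 1.049.

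The sign depends on which hands are more contaminated and which arm has more caregiver samples. The document settles neither.

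**5. Equal shares, true effect on child hands.** Pooled effect on the log scale = (1 − c) × child effect + c × caregiver effect. With c = 15%, a child effect of 0.30 log10 and no caregiver effect, this is 0.85 × 0.30 = 0.255. On the binary scale, take child prevalence 50%, caregiver prevalence 30%, a true child PR of 0.80 and no caregiver effect:
- c = 10%: 0.39/0.48 = 0.813.
- c = 20%: 0.38/0.46 = 0.826.
- c = 30%: 0.37/0.44 = 0.841.

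This dilution depends on there being no caregiver effect. On the log scale, an equal caregiver effect gives no dilution, and a larger one raises the pooled estimate above the child effect.

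**The case against.** The strongest reply is that the outcome was never strictly child hands. The outcomes section, the third secondary research question in the Background and the Discussion all speak of household contamination. For that construct, a ranked rule that yields one hand sample per household is coherent, and the mismatch shrinks to one sentence in the abstract. This stands in part: it limits the point to a reconciliation. It does not settle which definition governs, because the outcomes section leaves the person unnamed.

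A second reply is that pooling is inferred from silence. The sentence on separate models distinguishes sample types and does not forbid a person-sampled term, and a statistical analysis plan that is not shown may supply one. That is fair, and the absence of model detail is not the complaint. The complaint is that the article states a child outcome and also a rule that fills it with adult samples.

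A reader might go further and infer that the caregiver share will differ between arms and so produce a spurious intervention effect. The document does not support that. The fallback rule and the eligibility date are the same in both arms, and endline enumerators are not told village status, although the article concedes they may infer it. Availability and consent do arise after randomisation among participants who know their arm, so a difference is possible. No mechanism or figure shows one.

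Finally, restricting to children does not remove selection. If arm affected which children were available, a child-only analysis would still condition on that. This stands, and it is why the share by arm has to be reported.

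**Conclusion.** The point holds in a limited form. The article's statements about the hand outcome do not agree on whose hands are meant, and the analysis as written estimates a child/caregiver mixture rather than the child-hand effect named in the abstract. Some caregiver substitution at endline is likely, though its rate is unknown.

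The size and direction of any bias cannot be derived from the document. On assumed values it is modest: 0.05 to 0.10 log10 for a 10 to 20 point difference in share and a 0.5 log10 gap, and no false difference when shares are equal. Equal shares still leave the estimate different from the child effect unless the intervention acts equally on both kinds of hands. The primary outcome, the randomisation and the trial sample size are untouched. Severity: minor.

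**What to change.** Reconcile the abstract, the outcomes section, the collection rule and the analysis section:

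- Define the main hand outcome as *E. coli* on child hands, and fit both the binary and the log-concentration model to child samples.
- Use caregiver samples only in a separate analysis, or in a pooled sensitivity model with a term for the person sampled.
- Make sure the person sampled is recorded with every rinse, and report the caregiver share by arm.

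The sampling order need not change. The cost is a few sentences and a somewhat smaller sample for the child-hand models, in a component already limited by laboratory logistics. The child-only estimate still depends on which children were available and whose caregivers agreed, so it should be read alongside the caregiver share by arm.
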